## Materials and methods

### Research hypothesis

The nutritional status of patients aged 65 years and over admitted to the medical and surgical inpatient units of the participating hospitals evolves unfavourably from admission to discharge and may increase the length of stay, hospital mortality, and early readmission.

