### Aims

The main objective of this project is to assess the risk of malnutrition and nutritional status on admission and its evolution until discharge, in patients aged 65 and over admitted to medical and surgical units in hospitals of the Spanish National Health System. In addition, the aim is to respond to the following specific objectives:

To identify the incidence and prevalence of risk of malnutrition and the presence of malnutrition and associated factors on patient admission and discharge.To describe the evolution of nutritional status during patient hospitalization.To analyze the average length of stay, hospital mortality, and early readmission as a function of nutritional status at admission and the presence of dysphagia in the study cohort.To determine the incidence and prevalence of dysphagia and associated factors on admission and discharge.To determine satisfaction with the quality of patient nutrition at discharge, the type of hospital food service, and the characteristics of the hospital nutrition unit.

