### Variables and instruments

The study variables are organized into eight groups: i) Nutritional status; ii) Dysphagia; iii) Food quality and environment; iv) Socio-demographic variables; v) Clinical, functional, cognitive, and frailty variables; vi) Variables related to the risk profile; vii) Context variables; viii) Variables related to the care process.

Specifically, nutritional status and dysphagia are considered the main variables of the study. Likewise, the variables related to nutritional status are organized into:

Risk of malnutrition on admission: Malnutrition Universal Screening Tool (MUST) will be used to determine the risk of malnutrition. This questionnaire will measure current weight (kg), estimated weight three months ago (kg), height (cm), and Body Mass Index (BMI) (kg/m2). If height and weight cannot be measured or obtained, they will be estimated mid-upper arm circumference (MUAC) and calf circumference (CC) are set for weight and forearm length for height by the nutrition staff of each hospital. All patients included in the study will be assessed on admission, every 7 days, and at discharge.Diagnosis of malnutrition and degree of severity at admission: Global Leadership Initiative on Malnutrition (GLIM) criteria will be used for the population identified as high risk according to MUST. In addition, the following biochemical parameters will be collected: albumin, prealbumin CRP, CRP/prealbumin ratio, transferrin, total cholesterol, and the total number of lymphocytes. They will be collected on admission, every 7 days, and discharge provided that the minimum time for their re-determination has elapsed.Type of nutritional care established (according to risk and diagnosis of malnutrition): Includes aspects such as referral to the nutrition and dietetics unit, dietary adaptation according to alteration, nutritional supplementation, type of nutrition, or nutritional education. It will be recorded within 48 hours of admission, every 7 days and at discharge, and in case of any modification in the selected intervention, the starting date should be noted.Daily intake: a semi-quantitative questionnaire will be used to record the amount of intake made during the days of admission.

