#### Phase 2: Follow-up

Participants will be monitored every 7 days until they are discharged from the hospital. In this way, the researchers in charge will make a forecast of follow-up dates. In addition to the variables indicated, the nutritional care established will be adapted according to the evolution of the nutritional status and degree of dysphagia of the patient during their hospital stay, as part of the usual practice in each centre. On each occasion, a record will be kept of the person collecting the data.

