#### Phase 3: Situation on discharge

In addition to the variables indicated, on the day of discharge from the hospital, the daily intake record book will be collected and the food satisfaction survey will be provided. The variables related to the care process (days of stay, hospital mortality, and whether it was early readmission) will also be recorded.

Finally, the patient will be given the continuity of care report at discharge, drawn up by the responsible physician together with the nursing recommendations and information sheets on care related to malnutrition or dysphagia, as appropriate.

Data collection will be carried out electronically through Research Electronic Data Capture (REDCap) (www.prooject-redcap.org) [25,26]. This is a web application that allows the creation of electronic data notebooks for research projects and their online and offline collection from computers and other mobile devices. It also includes a scheduling and alarm system to manage data collection during monitoring. In this regard, it should be noted that the researchers who take on the data collection will receive training on the operation of REDCap and that a pilot of the process of recruiting participants and data collection will be carried out for one month.

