### Data analysis

A descriptive analysis of all the study variables will be carried out, using the appropriate measures according to the type of variable and their corresponding 95% CIs. Firstly, depending on the groups to be compared and compliance with the application requirements, a bivariate analysis will be performed, including the chi-squared or Fisher’s exact test (qualitative variables) and Student’s t-test, ANOVA, Mann-Whitney U-test, or Kruskal-Wallis (quantitative variables), depending on the application conditions.

For the analysis of the evolution of the risk of malnutrition, McNemar’s test or Cochran’s Q test will be used for qualitative variables and paired t-test or Friedman’s rank test for quantitative variables. The incidence of risk of malnutrition and undernutrition will be calculated, as for dysphagia, during the care process and at patient discharge, estimating their corresponding Odds Ratios and 95% CI using logistic regression models.

To assess the possible risk factors for both malnutrition and dysphagia and the socio-demographic and clinical characteristics of the patients, multivariate logistic regression models will be constructed. As independent variables will include: type of nutritional care established according to the risk of malnutrition; daily intake; suspected and diagnosed dysphagia and days of stay. As control variables will include: those related to the risk profile; sociodemographic (sex, age); clinical, functional, cognitive and frailty variables. In the case of mortality and time to readmission, multivariate Cox regression models will be fitted. Independent variables will be included: level of risk of malnutrition at admission; diagnosis of malnutrition at admission; change in risk of malnutrition at admission, at 7 days and at discharge; change in nutritional status at admission, at 7 days and at discharge. Control variables will include: type of nutritional care established (according to risk of malnutrition); daily intake; contextual; related to risk profile; sociodemographic; clinical, functional, cognitive and frailty variables; suspected and diagnosed dysphagia. In all multivariate models, possible interaction effects and possible collinearity will be analyzed.

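### The logistic risk-factor models use one predictor list with no time order for both malnutrition and dysphagia, so the odds ratios for nutritional care and days of stay would partly or wholly reflect reverse causation or indication

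*Protocol article*

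**What the plan says.** In the protocol article, Data analysis, the stated purpose of the multivariate logistic models is "To assess the possible risk factors for both malnutrition and dysphagia". One list of independent variables follows: "type of nutritional care established according to the risk of malnutrition; daily intake; suspected and diagnosed dysphagia and days of stay". The control variables are risk profile, sex and age, and clinical, functional, cognitive and frailty variables. Neither list gives a time point, names MUST or GLIM status at admission, or differs by outcome.

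Other sections fix how these predictors arise:

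- **Care.** Variables and instruments defines it as "Type of nutritional care established (according to risk and diagnosis of malnutrition". Under Phase 2: Follow-up, "the nutritional care established will be adapted according to the evolution of the nutritional status and degree of dysphagia of the patient".
- **Days of stay.** The Research hypothesis is that nutritional status "evolves unfavourably from admission to discharge and may increase the length of stay, hospital mortality, and early readmission". The third specific objective in Aims is "To analyze the average length of stay, hospital mortality, and early readmission as a function of nutritional status at admission and the presence of dysphagia". Phase 3: Situation on discharge states: "The variables related to the care process (days of stay, hospital mortality, and whether it was early readmission) will also be recorded".
- **Dysphagia.** Phase 1 sends patients with EAT-10 of 3 or more to MECV-V assessment.

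The first and fourth specific objectives seek factors associated with malnutrition and with dysphagia at admission as well as at discharge.

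**The concern.** A risk-factor model can be interpreted only if the predictors precede the outcome. Here care is a response to the outcome, and stay is elsewhere treated as a result of it. If both enter a model of malnutrition at admission, patients who received nutritional support and stayed longer will look as if support and stay were risk factors. Adjusting for effects of the outcome also pulls the odds ratios of real factors, such as dysphagia and frailty, away from their proper values.

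At stake are the associated-factor parts of the first and fourth specific objectives. The safeguards in the plan do not address this. Collinearity and interaction checks, mixed models for unit and hospital, and multiple imputation all leave the direction of time untouched.

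**Working it through.** The plan gives no figure on this point. Its sample size is not in question: 1.96² × 0.25 / 0.05² = 384.1, rounded up to 385; 385 / 0.85 = 453 per hospital; 9 × 453 = 4077.

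**Step 1. Time order, from the document.**

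| Predictor | When and why it arises | Outcome at admission | Incidence up to discharge |
|---|---|---|---|
| Care type | First recorded within 48 hours, set by malnutrition risk and diagnosis, later adapted | After the outcome | Can precede it, but chosen by baseline risk, which is not in the model |
| Daily intake | During the stay | After the outcome | Can precede it, if dated |
| Days of stay | Known at discharge | After the outcome | Partly time at risk, partly an effect of the outcome |
| Suspected and diagnosed dysphagia | Admission, every 7 days, discharge | Legitimate for malnutrition; for dysphagia it is the outcome itself | Same, unless it means baseline status |

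**Step 2. Spurious odds ratio for stay, closed form.** Assume log stay is normal with the same SD in patients with and without malnutrition, and that malnutrition multiplies stay by a ratio r. With no effect of stay on malnutrition, logistic regression returns OR per SD = exp(ln r / SD). The document gives neither r nor the SD, so both are assumptions:

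| r | SD 0.5 | SD 0.7 | SD 0.9 |
|---|---|---|---|
| 1.2 | 1.44 | 1.30 | 1.22 |
| 1.3 | 1.69 | 1.45 | 1.34 |
| 1.5 | 2.25 | 1.78 | 1.57 |

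For example, ln 1.3 = 0.262; 0.262 / 0.7 = 0.375; exp(0.375) = 1.45.

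**Step 3. Distortion of other factors, admission outcome (simulation, 400,000 patients, all effects assumed).** Malnutrition (28%) depends on dysphagia (true OR 2.0) and frailty. Care depends on malnutrition (OR 3 to 20) and dysphagia (OR 2). Log stay has SD 0.6 and rises by b = 0.1 to 0.4 with malnutrition, by 0.1 with dysphagia and by 0.1 per SD of frailty. Neither care nor stay affects malnutrition.

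- Without care and stay: dysphagia OR 1.99, frailty OR 1.64.
- With care and stay: dysphagia OR 1.16 to 1.68, frailty OR 1.46 to 1.60, care OR 3 to 20, stay OR 1.2 to 2.2 per doubling.

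Two of these results can be checked by hand. Stay per doubling is 2^(b/0.36), which is 1.21, 1.62 and 2.16 for b = 0.1, 0.25 and 0.4. Frailty is 1.64 × exp(−0.1b/0.36), which is 1.60, 1.53 and 1.47. Both agree with the simulation.

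**Step 4. Care in an incidence model (one assumed scenario).** Baseline risk raises the odds of receiving care by 20 and of the outcome by 4; care is truly protective, OR 0.70; incidence is about 15%. Without baseline risk in the model, the care OR is 1.57. With it, the OR is 0.70. This shows that the direction can reverse; it does not estimate the size in this study.

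**Step 5. Dysphagia as outcome.** Diagnosed dysphagia at the same assessment is the outcome. If MECV-V is done only after a positive EAT-10, as in Phase 1, no unsuspected patient can be a diagnosed case and the suspected-dysphagia odds ratio is infinite. Variables and instruments also says that both instruments are used in all patients, so this last result depends on the gated reading.

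**The case against.** - **The list may be a condensed pool for several models, with the dysphagia terms meant for malnutrition only.** That is plausible, and nowhere does the article say that dysphagia will be regressed on itself. Such a model would also fail visibly when fitted. This part is therefore a literal reading that needs clarification, not an established error. The care and stay problem does not depend on it.
- **The sentence before the list concerns incidence during the stay and at discharge, where care, intake and stay are sensible candidates.** This stands in part. Care recorded early, with start dates for changes, can precede incident malnutrition. The fault there is confounding by indication. However, Aims also seeks factors at admission, and the list is not limited to incidence.
- **Longer stays really do bring more incident cases.** This stands. At a constant daily risk, higher incidence in longer stays is genuine time at risk, and all patients are assessed at discharge. It argues for modelling time, not for treating the excess as an artefact.
- **A reader might infer that all reported risk factors would be artefacts.** The document does not support that. Age, sex, frailty and the other controls are distorted, not manufactured, and dysphagia is a legitimate predictor of malnutrition.

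**Conclusion.** The point holds in limited form. As written, the list would give care and stay odds ratios that reflect reverse causation in admission models. In incidence models, care would be confounded by indication, and stay would combine exposure time with an effect of the outcome. Dysphagia terms are at fault only in a dysphagia model, and only if the list is applied literally.

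The direction of the problem follows from the protocol's own definitions and timing. Its size does not: the range of 1.34 to 1.69 per SD for stay assumes a 30% longer stay and a log-SD of 0.9 to 0.5, and the simulated figures rest on assumed effects. The main objective is untouched, because it rests on prevalence, incidence and paired comparisons. The Cox models have their own list. The associated-factor parts of the first and fourth objectives depend on these models, so the list should be corrected before they are fitted.

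**What to change.** State separate covariate sets by outcome and time point:

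1. **Admission models.** Use only characteristics present at admission. Drop nutritional care, in-hospital intake and days of stay.
2. **Dysphagia outcome.** Remove suspected and diagnosed dysphagia at the same assessment from the predictors. If admission malnutrition is entered, report it as a cross-sectional association and show the model without it as well, since the Introduction says dysphagia can aggravate malnutrition.
3. **Incidence models.** Restrict to patients free of the condition at admission. Use care and intake recorded before the outcome assessment. Adjust for baseline MUST (and GLIM where available) in the malnutrition model, or admission EAT-10 status in the dysphagia model. Handle stay as time at risk, for example in a discrete-time model that allows a short last interval, and not as a risk factor.

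The cost is analysis wording and a little more modelling work. The 7-day assessments and care start dates are already planned, and the sample size does not change. The price is less intake information for short stays, where little intake precedes the outcome assessment.

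### The logistic risk-factor models for malnutrition name no admission nutritional status, so, applied to the stay or discharge, they can show admission associations as factors of in-hospital evolution

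*Protocol article*

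**What the plan says.** All references are to the protocol article.

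- **Aims.** The main objective is to "assess the risk of malnutrition and nutritional status on admission and its evolution until discharge, in patients aged 65 and over". The first specific objective is "To identify the incidence and prevalence of risk of malnutrition and the presence of malnutrition and associated factors on patient admission and discharge".
- **Variables and instruments.** On MUST: "All patients included in the study will be assessed on admission, every 7 days, and at discharge". GLIM is applied only to patients at high risk on MUST (a score of 2 or more, according to the Phase 1 section). EAT-10 and MECV-V are planned at both admission and discharge.
- **Data analysis, incidence.** Incidence is to be calculated "during the care process and at patient discharge, estimating their corresponding Odds Ratios and 95% CI using logistic regression models".
- **Data analysis, risk-factor models.** Their purpose is "To assess the possible risk factors for both malnutrition and dysphagia and the socio-demographic and clinical characteristics of the patients". The independent variables are "type of nutritional care established according to the risk of malnutrition; daily intake; suspected and diagnosed dysphagia and days of stay". The controls follow: "As control variables will include: those related to the risk profile; sociodemographic (sex, age); clinical, functional, cognitive and frailty variables".
- **Data analysis, Cox models.** For mortality and readmission, the covariates do include the admission risk level and the admission diagnosis of malnutrition.

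Admission nutritional status cannot easily be read into the clinical controls. Variables and instruments treats nutritional status as a group of its own, apart from the clinical, functional, cognitive and frailty group. The Phase 1 section gives diagnosis and renal or liver disease as the clinical variables, and places BMI, MUST and GLIM under other labels.

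**The concern.** Status at discharge depends heavily on status at admission. A model of discharge status without the admission value mixes two kinds of factor: those that patients brought with them, such as frailty or dependence, and those that changed their status in hospital. Because the study is about evolution, readers will be inclined to take the resulting odds ratios as factors of deterioration during the stay.

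There are two consequences, and they concern different factors:

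1. A factor linked to admission status, with no effect afterwards, shows a non-null discharge odds ratio.
2. A factor unrelated to admission status that does act during the stay is estimated with an odds ratio closer to 1 and tested with less power.

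For dysphagia the issue is different. A dysphagia variable is in the list of independent variables, but with no time point. If the concurrent value were entered in a model of dysphagia, the outcome would predict itself.

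**Working it through.** **The plan's own figure.** n = 1.96² × 0.5 × 0.5 / 0.05² = 384.1, rounded up to 385. Allowing for 15% losses, 385 / 0.85 = 452.9, so 453. Nine hospitals give 9 × 453 = 4077. The stated sizes are reproduced. Evaluable numbers are 385 per hospital and 9 × 385 = 3465 pooled.

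**Inputs from the article.** 26.9% malnourished on admission and 18% developing malnutrition in hospital (Introduction); two-sided 0.05 (Data analysis).

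**Assumptions, not in the article.** The 18% applies to patients free of malnutrition at admission. A proportion s of 60–90% of admission cases is still malnourished at discharge. The factor is binary, present in 50% of patients, with an admission odds ratio of 2 and no effect on change. There are no other covariates and no clustering.

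**Step 1: admission.** Find q0 and q1 (admission prevalence without and with the factor) such that (q0 + q1)/2 = 0.269 and the odds ratio is 2. Result: q0 = 0.202, q1 = 0.336.

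**Step 2: discharge.** d = q × s + (1 − q) × 0.18. For s = 0.80:
- d0 = 0.202 × 0.80 + 0.798 × 0.18 = 0.305
- d1 = 0.336 × 0.80 + 0.664 × 0.18 = 0.388
- OR = (0.388/0.612) / (0.305/0.695) = 1.45

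| Persistence s | d0 | d1 | Discharge OR | Significant, n = 385 | Significant, n = 3465 |
|---|---|---|---|---|---|
| 60% | 0.265 | 0.321 | 1.31 | 23% | 95% |
| 70% | 0.285 | 0.355 | 1.38 | 31% | 99% |
| 80% | 0.305 | 0.388 | 1.45 | 40% | >99% |
| 90% | 0.325 | 0.422 | 1.51 | 50% | >99% |

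With admission status in the model, the odds ratio is 1.00 and the rejection rate is 5%.

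**Sensitivity.**
- Admission odds ratio 1.5: discharge OR 1.17–1.28, significant in 11–21% (n = 385) and 58–94% (n = 3465).
- Factor present in 40% of patients, admission odds ratio 2, s = 70–90%: discharge OR 1.39–1.53.
- Admission prevalence 23.7% or 37% (both in the Introduction), admission odds ratio 2: discharge OR 1.29–1.48 or 1.35–1.60.

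**Step 3: restriction to patients free at admission.** About 3465 × (1 − 0.269) = 2533 pooled patients, with 2533 × 0.18 = 456 new cases, would remain. In the two-state model this removes the effect in step 2. It need not do so fully if risk differs by MUST score. Suppose 25% of those free at admission score MUST 1, with three times the incidence of MUST 0. The incidences are then 0.18/(0.75 + 0.25 × 3) = 12% and 36%. A factor present in 40% and linked to MUST 1 with an odds ratio of 2 or 3 then shows an incidence odds ratio of 1.24 or 1.40 with no effect of its own. The MUST 1 inputs are assumed, and the 18% concerns malnutrition, not a MUST threshold, so this is only illustrative.

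**Step 4: power, for a factor unrelated to admission status.** Power = Φ(ln OR / SE − 1.96). At n = 3465, conditional OR 1.25 and s = 80%:
- without admission status, OR 1.160 and SE 0.071: power 55%
- with admission status, OR 1.250 and SE 0.088: power 72%

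Over s = 60–90%, power is 43–70% without and 66–78% with admission status. At n = 385 and OR 1.8 it is 35–58% without and 54–66% with.

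**The case against.** Several points on the other side have force.

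- **Time point.** A reader might infer that the covariate list is expressly for discharge models. It is not: the sentence introducing the list gives no time point, and discharge appears in the preceding sentence, on incidence. This stands, so the point is conditional. Discharge is nonetheless within the objectives, and days of stay and daily intake make sense as predictors only for an outcome during or after the stay.
- **Is the odds ratio wrong?** A reader might call the 1.3–1.5 spurious. For prevalence at discharge it is a real association, and the first specific objective asks for such factors. It misleads only when read as a factor of evolution. Adjusting for admission status changes the question that the odds ratio answers.
- **Main objective.** Overall change is also tested with McNemar, Cochran's Q, paired t and Friedman methods, which use the admission value within patient. That stands. What is affected is the attribution of change to factors.
- **Dysphagia.** A reader might say its baseline is missing too. The listed dysphagia variable may be the admission value, so only the missing time point can be faulted.
- **Condensed article.** The lists are not declared exhaustive, and care type, set according to malnutrition risk, is a partial proxy for admission status. But the Cox list in the same section names admission status explicitly, so the contrast lies in stated text. A proxy recorded after admission and open to modification does not replace the score.
- **Power.** The study is sized on precision and a variables rule, not on power, so no stated target is missed. The power loss is secondary.

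**Conclusion.** The point holds for malnutrition, in conditional form. Where the logistic risk-factor models are applied to status during the stay or at discharge, they name no admission nutritional status, and a factor linked only to that status can be taken for a factor of evolution. For an admission odds ratio of 2 the discharge odds ratio is about 1.3–1.5, significant in roughly a quarter to a half of single-hospital analyses and in about 95% or more of pooled ones. Persistence, factor frequency and the admission odds ratio are assumptions. As long as admission cases are more often malnourished at discharge than others, they set the size of the effect and not its direction. Adjusting for related controls or allowing for clustering would alter the rejection rates.

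The loss of power is a separate effect on other factors, and its size depends on the assumed persistence. For dysphagia, only the missing time point is at fault. The documents do not support saying that every logistic model is wrong: models of status at admission need no change.

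**What to change.** In Data analysis, state the outcome time point and the at-risk set of each logistic model, and add:

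- For malnutrition risk or malnutrition at discharge, when modelled to study evolution, include the admission MUST score as a covariate, and admission GLIM status with patients at MUST below 2 coded as not malnourished. The coding is needed because GLIM is applied only at MUST 2 or more.
- Restrict incidence models to patients free of the condition at admission, and still adjust for the admission MUST score.
- For dysphagia outcomes, use the admission EAT-10/MECV-V value as the covariate, not the concurrent one.
- Leave models of status at admission as they are.

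The cost is a few sentences and no new data collection. One or two of the 20 planned model variables are used, and the odds ratios must be reported as conditional on admission status. If the association with discharge prevalence is also wanted, it can be reported without the admission term and labelled as such.
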